## Abstract

**Background:**

It is known that only 50% of patients diagnosed with major depressive disorders (MDD) respond to the first-line antidepressant treatment. Accordingly, there is a need to improve response rates to reduce healthcare costs and patient suffering. One approach to increase rates of treatment response might be the integration of pharmacogenetic (PGx) testing to stratify antidepressant drug selection. The goal of PGx assessments is to identify patients who have an increased risk to experience adverse drug reactions or non-response to specific drugs. Especially for antidepressants, there is compiling evidence on PGx influencing drug exposure as well as response.

**Methods:**

This study is an open-label, randomized controlled trial conducted in two study centers in Switzerland: (1) the Psychiatric Clinic of Solothurn and (2) the Private Clinic Wyss in Münchenbuchsee. Adult inpatients diagnosed with a unipolar moderate or severe depressive episode are recruited at clinic admission and are included in the study. If the adjustment to a new antidepressant pharmacotherapy is necessary, the participants are randomized to either Arm A (intervention group) or Arm B (control group). If no new antidepressant pharmacotherapy is introduced the participants will be followed up in an observational arm. The intervention is the service of pharmacist-guided pre-emptive PGx testing to support clinical decision making on antidepressant selection and dosing. As a comparison, in the control group, the antidepressant pharmacotherapy is selected by the treating physician according to current treatment guidelines (standard of care) without the knowledge of PGx test results and support of clinical pharmacists. The primary outcome of this study compares the response rates under antidepressant treatment after 4 weeks between intervention and control arm.

**Discussion:**

The findings from this clinical trial are expected to have a direct impact on inter-professional collaborations for the handling and use of PGx data in psychiatric practice.

**Trial registration:**

ClinicalTrials.govNCT04507555. Registered on August 11, 2020. Swiss National Clinical Trials Portal SNCTP000004015. Registered August 18, 2020.

## Administrative information

Note: the numbers in curly brackets in this protocol refer to SPIRIT checklist item numbers. The order of the items has been modified to group similar items (see http://www.equator-network.org/reporting-guidelines/spirit-2013-statement-defining-standard-protocol-items-for-clinical-trials/).

## Introduction

### Background and rationale {6a}

Successful treatment of depression remains challenging, considering the fact, that only 50% of patients suffering from major depressive disorders respond to the first-line antidepressant treatment [1, 2]. Furthermore, a drug exposure of at least 4 weeks is necessary to assess clinical treatment response [3], possibly making the trial and error approach time-consuming and exhausting for the patient.

It is well known that patients are exhibiting diverse reactions following drug intake. In many cases, inter-individual variability in drug response can be attributed to changes in systemic drug exposure (area under the curve). Meaning the risk of low-drug serum levels resulting in treatment failure and high-drug serum levels leading to toxicity. The organism influences systemic drug exposure by multiple mechanisms namely absorption, distribution, metabolism, and excretion (ADME) of a taken drug molecule. This concept is summarized in the term of pharmacokinetics and comprises a variety of proteins acting on drug molecules in terms of transport (absorption, distribution, and excretion) as well as enzymatic reactions (metabolism). Changes in the activity of the aforementioned proteins will therefore affect systemic exposure and hence drug response. Moreover, the activity of drug transporters and enzymes is influenced by avoidable factors such as drug-drug interactions or drug-food interactions, but also by given predispositions including disease factors and genetics. In fact, a wide range of genes encoding drug transporters and enzymes are polymorphs, occasionally translating into proteins with altered activity [4].

A relevant drug-gene interaction is for example *CYP2D6* with tricyclic antidepressants. The gene encoding for the cytochrome P450 enzyme 2D6 is known to be highly polymorphic including variants that are translated into metabolizing enzymes with increased or reduced activity. Associated phenotypes are termed as ultra-rapid metabolizer or poor metabolizer, respectively [5]. Tricyclic antidepressants are often metabolized via CYP2D6 and have repeatedly been associated with altered pharmacokinetics due to the individual’s genetic predisposition. Based on the rich data on pharmacogenetics, a CPIC (Clinical Pharmacogenetics Implementation Consortium) guideline was published with recommendations for tricyclic antidepressant dosing and for compound selection based on the respective CYP2D6 metabolizer status [6]. Nevertheless, sparse evidence from prospective trials in terms of therapy outcome and cost-effectiveness has so far been an obstacle for implementing *CYP2D6*-guided tricyclic antidepressant prescribing in clinical practice [7].

Remarkably, a wide range of studies is currently being conducted with the aim to identify biomarkers for early and reliable prediction of treatment outcomes of marketed antidepressants, e.g., [8, 9]. However, there is already compiling evidence on pharmacogenetics influencing both, antidepressant exposure and treatment response. This data is gathered and rated according to its level of evidence in the Pharmacogenomics Knowledge Base (PharmGKB) [10]. The aforementioned Clinical Pharmacogenetics Implementation Consortium (CPIC, https://cpicpgx.org/) and the Dutch Pharmacogenetics Working Group (DPWG, https://www.knmp.nl/patientenzorg/medicatiebewaking/farmacogenetica) are publishing guidelines on genotype-guided drug dosing and/or drug selection, which currently includes recommendations for tricyclic antidepressants and selective serotonin reuptake inhibitors. Besides, the Swiss Society for Anxiety and Depression (SGAD) recommends genotyping of *ABCB1* upon antidepressant treatment failure [3]. The latter gene encodes for p-glycoprotein an efflux transporter known for its function in the extrusion of drug molecules and xenobiotics at the blood-brain barrier. Even if not fully validated, it has been hypothesized that patients carrying the wildtype allele of the transporter exhibit increased efflux of substrate antidepressant drugs at the blood-brain barrier, which would translate into decreased drug levels within the central nervous system, and therefore at the place of action. This assumption is based on a limited number of studies, where the *ABCB1* genotype was linked to antidepressant treatment response [11–13].

Even though pharmacogenotyping is not part of routine patient care, pharmaceutical companies cite the known influence of certain polymorphisms on serum levels, adverse drug reactions, and treatment failure in their drug labels [14]. This also applies to several antidepressants authorized in Switzerland namely the tricyclic antidepressants clomipramine, amitriptyline, nortriptyline, and opipramol; the selective serotonin reuptake inhibitors escitalopram, citalopram, fluoxetine, paroxetine, and fluvoxamine; the monoamine oxidase A inhibitor, moclobemide, and the serotonin; and noradrenaline reuptake inhibitors venlafaxine and duloxetine, to name some of them.

Today, pharmacogenetic panel tests are commercially offered. These panel tests consider multiple polymorphic genes involved in pharmacokinetics as well as in the pharmacodynamics of antidepressant drugs. Stratipharm® (humatrix AG, Pfungstadt Germany, https://www.stratipharm.de) is one of the commercial products offering pharmacogenetic panel testing from buccal swabs combined with an evidence-based genotype interpretation. Hitherto, there is only a limited number of prospective clinical studies and to our knowledge non conducted in Switzerland, testing the influence of pre-emptive pharmacogenotyping on patient outcome, whereby limiting the evidence for being advantageous for depression remission or cost-effectiveness over the standard of care, e.g., [15–17]. In fact, pre-emptive panel testing is not yet state of the art in psychiatric practice.

### Objectives {7}

We hypothesize that it is beneficial to incorporate PGx information to guide drug selection and dosing in the treatment of depression, involving clinical pharmacists in processing and evaluating the PGx test results in the context of the individual patient history and current co-medication.

The primary objective of this clinical study is to compare the service of pharmacist-guided PGx testing with the current standard of care for antidepressant selection and dosing with regard to treatment outcome. Accordingly, the following null hypothesis results for the primary endpoint: Therapy response rates after antidepressant treatment for 4 weeks do not differ whether the service of pharmacist-guided pre-emptive pharmacogenetic testing was applied or not.

The secondary objectives are to compare tolerability of the antidepressant pharmacotherapy and overall duration of hospitalization between the intervention and standard care study arms.

### Trial design {8}

This is an open-label, randomized controlled trial, investigating the effectiveness and tolerability of registered antidepressants in adult inpatients with diagnosed major depressive episode.

To prevent selection bias, eligible patients in need of a new antidepressant pharmacotherapy are randomized at the same ratio into either the control or the intervention arm (parallel study arms).

## Methods: Participants, interventions, and outcomes

### Study setting {9}

This is a multicenter clinical trial conducted in Switzerland, at the Psychiatric Clinic of the Solothurner Spitäler AG in Solothurn and the Private Clinic Wyss in Münchenbuchsee.

### Eligibility criteria {10}

Patients are considered eligible for trial inclusion if all of the following criteria are met: (1) ≥ 18 years old, (2) diagnosis of unipolar moderate or severe depressive episode (ICD10: F32.1/32.2/33.1/33.2), and (3) Hamilton Depression Rating Score, version 17 items (HAM-D17) ≥ 17.

If a patient meets any of the following criteria, he or she cannot be included in the trial: (1) acute suicide risk, (2) psychotic symptomatology, (3) other acute serious psychiatric disorder other than depression, (4) excessive consumption of alcohol and/or drugs, (5) severe acute or severe chronic somatic diseases, (6) pregnant or lactating women, and (7) under current treatment with fluoxetine.

### Who will take informed consent? {26a}

The investigators will explain to each participant the nature of the study, its purpose, the procedures involved, the expected duration, the potential risks and benefits, and any discomfort it may entail. Each participant will be informed that the participation in the study is voluntary and that he or she may withdraw from the study at any time and that withdrawal of consent will not affect his or her subsequent medical assistance and treatment. All participants of the study will be provided a participant information sheet and a consent form describing the study and providing sufficient information for participants to make an informed decision about their participation in the study. Participants will be granted enough time to decide whether to participate or not. The formal consent of a participant, using the approved consent form, will be obtained before the participant is submitted to any study procedure. The consent form will be signed and dated by the investigator or his designee at the same time as the participant^1^.

### Additional consent provisions for collection and use of participant data and biological specimens {26b}

With an additional consent form, the patient is asked for permission for further use of the collected biological samples and genetic data, in encrypted form, for not yet further defined future research projects. If the patient consents to the further use of the biological samples and genetic data, the remaining biological material is stored in the Biobank Biopharmazie at the University of Basel, Switzerland.

### Interventions

#### Explanation for the choice of comparators {6b}

The intervention described in the following section {11a} is compared with the current standard of care, where the treating investigator alone selects and doses the antidepressant pharmacotherapy, considering clinical factors only, without taking genetics into account.

#### Intervention description {11a}

The study intervention is the service of pharmacist-guided pre-emptive PGx testing to support clinical decision making for antidepressant selection and dosing.

This service involves genotyping and thereof evidence-based genotype interpretation commercially offered as Stratipharm® (humatrix AG, Pfungstadt Germany, https://www.stratipharm.de). Stratipharm® provides substance-specific recommendations based on current evidence of international guidelines (Clinical Pharmacogenetics Implementation Consortium, CPIC, and Dutch Pharmacogenetics Working Group, DPWG) as well as evidence from clinical studies annotated in the Pharmacogenomics Knowledge Base (PharmGKB, www.pharmgkb.org). Furthermore, clinical pharmacists will process and evaluate the results from PGx testing (Stratipharm®) in the context of the individual patient medication history, medical, and laboratory data (including drug serum levels if available) as well as current co-medication (drug-drug interactions) and forward an individualized recommendation for antidepressant selection and dosing to the treating physician. This intervention is applied pre-emptively, meaning before initiation of a new antidepressant pharmacotherapy during the first week after inclusion into the study.

#### Criteria for discontinuing or modifying allocated interventions {11b}

The intervention under investigation is the service of pharmacist-guided pharmacogenetic testing for the selection and dosing of a new antidepressant pharmacotherapy. Discontinuation or modification of the investigator’s chosen drug and dosage due to any reason is not impaired by the allocated intervention.

#### Strategies to improve adherence to interventions {11c}

The study is conducted on inpatient depression wards of the psychiatric clinics, where monitoring of medication intake and basic laboratory tests (hematology, clinical chemistry, and the like) are part of the routine clinical practice. Furthermore, a clinical study coordinator is supporting the investigators in the conduct of all study-specific assessments, which are internally monitored.

#### Relevant concomitant care permitted or prohibited during the trial {11d}

The introduction of a new antidepressant pharmacotherapy or augmentation strategy (e.g., lithium and the like) are not possible until after randomization when genotyping results are available (7±2 days after inclusion). However, the following measures can be taken in the interim: (1) if an antidepressant therapy has already been taken before entering the clinic, it can be continued during this period, and (2) additional supportive measures are possible, including sleep-promoting pharmacotherapy (e.g., benzodiazepines or low-dose trazodone, mirtazapine, trimipramine).

#### Provisions for post-trial care {30}

After the intervention phase of the study, patients in the control and observation groups as well as their treating physicians will gain access to the PGx data collected.

Study participants do not receive any compensation. However, there are no additional costs for the study participants or the respective health insurance company due to study participation.

In the event of study-related damage or injuries, the liability of the respective institution, Psychiatric Services Solothurn or Private Clinic Wyss, provides compensation, except for claims that arise from misconduct or gross negligence.

#### Outcomes {12}

The primary endpoint is defined as the rate of response to the antidepressant therapy at the end of week 4 of the treatment phase. This time point was chosen based on the recommendations of the SGAD, which advise to assess clinical effectiveness after four weeks of antidepressant pharmacotherapy [3]. Moreover, the response is determined as a reduction in the Hamilton Depression (HAM-D) Scale score of at least 50% from the baseline score [18]. In this study, the 17-item HAM-D questionnaire (HAM-D17) is used.

Secondary endpoints will be assessed to further evaluate the clinical effectiveness of pharmacist-guided PGx testing as an intervention in antidepressant pharmacotherapy. Included are the following endpoints: (1) time to response—time span from the start of antidepressant pharmacotherapy until first assessed response (= HAM-D17 reduction of at least 50% compared to baseline), until end of week 4; (2) remission rate—HAM-D17 score ≤ 8, at week 4; (3) overall change in HAM-D17 score from baseline to end of week 4; (4) time till discharge—time span from admission to discharge from inpatient treatment, assessed up to 3 months; (5) patient depression self-rating—two weekly assessment with Beck-Depression-Inventory (BDI-II) questionnaire [19], until end of week 4; (6) side effect measure—weekly assessment of self-rated frequency, intensity, and burden of side effects (FIBSER score) [20], until end of week 4; and (7) Number of AEs related to antidepressant pharmacotherapy—severity grading ≥ 2 (using CTCAE version 5.0) [21] and causality to antidepressant pharmacotherapy assessed as possible, probable, or definite, until end of week 4.

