##### Randomization and procedures for arms A and B

If after the run-in phase, at day 0 (±3 days), the treating physician assesses the adjustment to a new antidepressant pharmacotherapy as necessary, and the patient is randomized to either arm A (intervention group) or arm B (control group) (see Fig. 1).

In arm B, the treating physician alone, according to the current standard of care considering clinical factors only, will determine the selection and dosing of the new antidepressant pharmacotherapy. The treating physician and patient will be blinded to the results of the previously conducted pharmacogenotyping for patients randomized to arm B until day 28. For patients in arm B, results from prior pharmacogenetic testing will be interpreted by a clinical pharmacist and made accessible to the treating physician after day 28.

In arm A, a clinical pharmacist will process and evaluate the results from PGx testing (Stratipharm®) in context of the individual patient history as well as current co-medication and forward an individualized recommendation for antidepressant selection and dosing to the treating physician at day 0.

In both arms, the newly prescribed antidepressant pharmacotherapy intake is continuously documented and therapy response observed over a period of 28 days with weekly assessments of adverse events related to the antidepressant medication (using CTCAE version 5.0) and scorings of HAM-D17 (days 0, 7, 14, 21, and 28; ±3 days) as well as patient self-assessments of FIBSER score (days 0, 7, 14, 21, and 28; ±3 days) and BDI-II score (days 0, 14, and 28; ±3 days) (see Table 1).

If patients in either study group remain in the clinic after day 28 (±3 days), a weekly follow-up of HAM-D17, FIBSER, and two-weekly BDI-II are continued until discharge (see Table 1).

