#### Plans to promote participant retention and complete follow-up {18b}

Assessments and follow-ups are only conducted during the participants’ inpatient stay at the psychiatric clinic. Therefore, the risk of loss to follow-up and deviation to the protocol due to failure to comply with the study visits are considered negligible. However, patients who withdraw their consent (e.g., refuse further data collection) will be informed that all data collected until the time point of their withdrawal will be kept coded and used for analysis.

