### Statistical methods

#### Statistical methods for primary and secondary outcomes {20a}

The primary outcome of this study is the response rate at day 28 in study arms A and B. The response is defined as a reduction of the HAM-D17 score of at least 50% compared to baseline at day 0. Additionally, the following secondary outcomes are assessed: time to response, remission rate, overall change in HAM-D17 score, laytime in the clinic, change in BDI-II score, change in FIBSER score, and number of AEs related to antidepressant pharmacotherapy. For statistical analyses, the software packages of “IBM SPSS Statistics” and “GraphPad Software” are used. A descriptive statistics analysis for all variables is performed. Fisher’s exact test or *t* test is used to compare pairwise differences between groups and between baseline and follow-up visits as per data type. To measure the correlation between variables, the Spearman coefficient will be used. Significance level is two-sided, *α* = 0.05. For further statistical analyses, adjustments for confounding factors will be taken into account. Any deviation from the original statistical plan will be described and justified in the final trial report.

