#### Methods in analysis to handle protocol non-adherence and any statistical methods to handle missing data {20c}

Missing data will be retrospectively retrieved from medical records if possible. If the missing data cannot be retrieved, the last observed value will be used for analysis. Study drop-outs are replaced to achieve the final calculated study size of 95 patients per study arms A and B.

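### Discharge before day 28 cuts short the count of adverse events, and the tests named take no account of time observed, so the AE comparison is biased if early discharge differs by arm

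*Protocol article*

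**What the plan says.** The last secondary endpoint in Outcomes {12} of the protocol article is "Number of AEs related to antidepressant pharmacotherapy", restricted to severity grade 2 or higher and to "causality to antidepressant pharmacotherapy assessed as possible, probable, or definite, until end of week 4". It is worded as a number, with no denominator of patient-time.

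The retention section {18b} states: "Assessments and follow-ups are only conducted during the participants’ inpatient stay at the psychiatric clinic". The section on procedures for arms A and B plans weekly AE assessment over 28 days and makes later follow-up conditional on the patient still being in the clinic. Table 1 also schedules an AE assessment at discharge.

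The statistical methods section {20a} names two tests for group comparisons, Fisher's exact test and the t test. One of them "is used to compare pairwise differences between groups and between baseline and follow-up visits as per data type". The section on additional analyses {20b} says that no adjusted analyses are currently planned.

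Length of stay is itself compared between the arms: it is a secondary objective in Objectives {7} and appears among the endpoints as "time till discharge—time span from admission to discharge from inpatient treatment, assessed up to 3 months".

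**The concern.** The window in which AEs are counted closes at day 28 or at discharge, whichever comes first. The second limit depends on something the service may change. A patient who leaves on day 14 is observed for half of the window, and one who leaves on day 21 for three quarters. If such patients are more frequent in one arm, that arm's AE number falls without any difference in tolerability.

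Tolerability and duration of stay are the two secondary objectives. Where early discharge differs by arm they would not be independent evidence, because part of an apparent AE benefit would be the shorter stay seen a second time. The bias can go either way. If the control arm left earlier, the intervention arm would show a spurious excess, and the interim analysis section {21b} gives an increased number of AEs as its example of a reason to stop the study.

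**Working it through.** **The plan's own figure.** The article gives no figure for the AE endpoint. Its one computed figure is the primary-endpoint sample size in {14}: 95 per arm for response 0.5 v 0.7, 80% power and alpha 5%. The usual two-proportion formula with pooled variance and no continuity correction gives 93 per arm, and the power at 95 is 80.8%. The figure is reproduced closely enough. It enters below only as the arm size.

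**Inputs.** From the article: a 28-day window, observation only as an inpatient, 95 per arm, and a two-sided 5% level. Assumed, because the article does not give them: the proportion *f* of an arm discharged early, the day *d* of that discharge, and an equal true AE rate in both arms.

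**Step 1: expected counts with a constant AE rate.** Mean observed days = (1 − *f*) × 28 + *f* × *d*. With equal true rates, the expected count ratio A/B equals the ratio of mean observed days. The last column is the share of 10,000 simulated trials (Poisson counts, mean 1 AE per 28 days) in which a t test on the counts rejects.

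| Early discharge, A v B | Day | Mean days, A v B | Count ratio | t test rejects |
|---|---|---|---|---|
| none | – | 28.0 v 28.0 | 1.00 | 5% |
| 20% v 10% | 21 | 26.6 v 27.3 | 0.97 | 5% |
| 30% v 10% | 21 | 25.9 v 27.3 | 0.95 | 6% |
| 30% v 10% | 14 | 23.8 v 26.6 | 0.89 | 11% |
| 50% v 10% | 14 | 21.0 v 26.6 | 0.79 | 31% |

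For example, 0.7 × 28 + 0.3 × 14 = 23.8, 0.9 × 28 + 0.1 × 14 = 26.6, and 23.8 / 26.6 = 0.89. The rejection rates depend on the assumed AE frequency. For 30% v 10% on day 14 they run from 8% at 0.5 AEs per 28 days to 17% at 2. Over-dispersed counts lower them.

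**Step 2: Fisher's exact test on patients with any AE.** With Poisson events at 1 per 28 days, the chance of at least one AE is 1 − e^(−1) = 0.632 over 28 days and 1 − e^(−0.5) = 0.393 over 14. For 50% v 10% leaving on day 14, the proportions are 0.5 × 0.632 + 0.5 × 0.393 = 0.513 and 0.9 × 0.632 + 0.1 × 0.393 = 0.608, a ratio of 0.84. Fisher's test on proportions carries the same kind of bias.

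**Step 3: AEs that cluster early.** Suppose 70% of AEs fall in weeks 1 and 2, and 15% in each of weeks 3 and 4. The expected count is then proportional to 1 − *f* × (share of AEs falling after discharge).
- 30% v 10% on day 21: 0.955 / 0.985 = 0.97
- 30% v 10% on day 14: 0.91 / 0.97 = 0.94
- 50% v 10% on day 14: 0.85 / 0.97 = 0.88

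**Step 4: whether AEs per patient-day would cure it.** With a constant rate, yes: the ratio returns to 1.00. With early clustering it over-corrects. For 50% v 10% on day 14, the rate ratio is 0.876 / 0.789 = 1.11. For 30% v 10% it is 0.938 / 0.895 = 1.05.

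Comparing within study time removes this. In weeks 3 and 4 of the 50% v 10% case, arm A has 0.30 × 0.5 AEs over 14 × 0.5 days, and arm B has 0.30 × 0.9 over 14 × 0.9. Both give 0.30 / 14 = 0.021 per day, a ratio of 1.00.

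**The case against.** The strongest reply is that the endpoint is capped at the end of week 4. A reader might infer that any shortening of the stay lowers the AE number. The documents do not support that. Stay is measured from admission and assessed up to 3 months, so the arms can differ in stay while every patient completes the 28-day window. Only a difference in discharge before day 28 matters, and the article does not say how often that occurs. It calls loss to follow-up negligible. That statement, however, concerns failure to comply with visits and does not address discharge. This objection limits the point but does not remove it.

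Second, the test sentence in {20a} is generic. It does not assign the t test to AEs, and an analysis plan that is not shown could add a rate. That is fair. But neither named test uses observation time, Step 2 shows that Fisher's test is affected too, and nothing in the article points to an exposure-based analysis.

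Third, a reader might infer from {20c}, under which "the last observed value will be used for analysis", that AE counts are formally carried forward as if no events followed discharge. That section does not mention AEs, and it first seeks missing data in the medical records. The point does not need this reading, because a plain count has the same effect. It is also unclear whether patients discharged early would be replaced as drop-outs under {20c}.

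Fourth, a reader might object to a t test on skewed, over-dispersed counts as such. The calculations do not bear that out: with equal observation in both arms, simulated over-dispersed counts kept the false-positive rate at about 5%.

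Finally, tolerability is also measured by the weekly FIBSER score, which is not a cumulative count.

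**Conclusion.** The point holds in conditional form. As written, the plan counts AEs over a period that discharge can cut short and compares the arms without regard to time observed. If discharge before day 28 differs by arm, the arm that leaves earlier shows fewer AEs at the same underlying rate.

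The size rests on assumed discharge patterns. It is nil if nobody leaves before day 28 or if early discharge is equal in the two arms. It is 3 to 5% for modest differences at day 21, and 11 to 21% for the day-14 differences examined under a constant AE rate. Early clustering of AEs reduces the last two to about 6 and 12%. The primary endpoint is not touched by this point. It is a worthwhile improvement to one secondary endpoint, not a threat to the trial's main conclusion.

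**What to change.** Define the AE period as day 0 to the earlier of day 28 or discharge, and analyse AEs over the time observed with a method that does not assume a constant hazard. Either of these will do:

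- time to first related AE of grade 2 or higher, censored at the earlier of day 28 or discharge; or
- a count model by study week, with the log of observed days in that week as offset, week as a factor, and standard errors that allow for several weeks per patient.

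Do not rely on a single offset for total days, for the reason shown in Step 4. State that days after discharge are unobserved and are not to be treated as free of AEs. Report observed days and the number discharged before day 28 by arm.

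The cost is small. AEs are already assessed weekly and at discharge, and time to discharge is already an endpoint, so no visit is added. The price is some extra analysis and an assumption to be stated openly: that discharge carries no information about later AEs, given arm and time since day 0.
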